### Muscle thiols and OXS markers

Muscle samples will be homogenized in phosphate buffer saline (PBS) containing protein inhibitors as described previously [54]. After homogenization, the samples will be centrifuged (12,000 g, 4 °C, 30 min) and the supernatant will be collected. GSH, GSSG, PC and MDA levels will be measured as indices of muscle’s redox status. All measurements will be performed spectophotometrically (Hitachi UV/VIS; Hitachi Instruments Inc., Tokyo, Japan) as described elsewhere [54]. All assays will be performed in duplicate.

### Statistical analyses and Power calculation

A preliminary power analysis (based on previous studies that used NAC administration to investigate its effects on EIMD), using the G*Power 3.0.10 program, showed that a minimum number of 10 participants per group is needed to obtain statistical meaningful results among repeated measurements [30]. Specifically, power calculation was performed for a two-way repeated-measures analysis of variance (ANOVA), within-between interaction test and input variables included: effect size, 0.55; α error, 0.05; power, 0.95; number of groups (LR and HR), 2; correlation among repeated measures, 0.5 and non-sphericity correction, 1. However, the total number of participants depends also on potential dropouts according to the following formula: *n* ’  = n/(1 − d) [55].

Thus, the final number of participants to be recruited with a dropout rate of 15% would be *n*’ = 10/(1–0.15) = 11.8. Therefore, ≥ 12 participants per group (LR vs HR) will be selected from the initial sample (*N* = 40–60) via k-means clustering to participate in the clinical trial (NAC vs placebo).

A k-means cluster analysis will be utilized to efficiently define two separate groups of subjects (LR and HR groups) from the total sample (*N* = 40–60), based on the SCs content of their vastus lateralis muscle of their dominant leg [24]. This type of analysis requires a relatively large initial sample size (*N* = ≥ 40), is a form of partitional clustering and is a multivariate method used to identify homogeneous groups (i.e., clusters) of cases based on a common trait [29, 56].

All analyses and reporting of the results will comply with the Standard Protocol Items: Recommendations for Interventional Trials (SPIRIT) Statement for reporting randomized clinical trials (RCTs) [57]. Results of participant’s baseline characteristics and outcome variables (primary, secondary and other) will be summarized using descriptive statistics and will be expressed as mean (standard deviation) or median (range) for continuous variables. Data normality will be examined using the Kolmogorov-Smirnov and the Shapiro-Wilk tests. If our data sets follow normal distribution, parametric tests will be applied. Baseline comparisons on the LR and HR groups (anthropometrics, body composition, strength, VO_2max_, dietary profile, PA) will be performed using a one-way ANOVA test. Time- and trial-effect comparisons within and between trial (NAC or placebo) in the LR and HR groups will be analyzed using a two-way repeated-measures ANOVA test with a Bonferroni correction for pairwise comparisons. If the data normality is violated, non-parametric tests will be applied. Baseline comparisons on the LR and HR groups will be performed using a Kruskal-Wallis test. Time-effect comparisons within trial (NAC or placebo) in the LR and HR groups will be analyzed using a Friedman test accompanied by Wilcoxon signed-rank test for pairwise comparisons. Trial-effect comparisons between trials (NAC vs placebo) in the LR and HR groups will be analyzed using a Kruskal-Wallis test accompanied by a Mann-Whitney *U* test for pairwise comparisons. Pearson’s correlation analysis will also be used to examine possible relations among variables. Correlation coefficients of r < 0.2, 0.2 < r < 0.7 and r > 0.7 will be defined as small, moderate and high, respectively. The level of statistical significance will be set at *p* < 0.05. Effect sizes (ES) and confidence intervals (95% CI) will be calculated on results of all dependent variables using the Hedge’s *g* method, corrected for bias. ES will be interpreted as none, small, medium-sized and large for values 0.00–0.19, 0.20–0.49, 0.50–0.79 and ≥ 0.8, respectively. Multiple-imputation analysis will also be utilized to handle missing data during data collection and sensitivity analyses will be executed to evaluate the robustness of the results [58]. Statistical analyses will be performed using the SPSS 20.0 software (IBM Corp., Armonk, NY, USA).

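### The power calculation is for an LR/HR interaction that the analysis does not plan, and its listed inputs do not yield 10 per group

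*Protocol article*

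**What the plan says.** All of this is in the Protocol article, Statistical analyses and Power calculation, unless stated otherwise.

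- **Result of the calculation.** It "showed that a minimum number of 10 participants per group is needed to obtain statistical meaningful results among repeated measurements". Dividing by 1 − 0.15 raises this to at least 12 per LR/HR group.
- **Test sized.** The "power calculation was performed for a two-way repeated-measures analysis of variance (ANOVA), within-between interaction test" is named, with "number of groups (LR and HR), 2".
- **Other inputs.** "effect size, 0.55"; "α error, 0.05"; power 0.95; "correlation among repeated measures, 0.5 and non-sphericity correction, 1". The number of measurements, the within factor and the effect-size metric are not given.
- **Analysis planned.** "Time- and trial-effect comparisons within and between trial (NAC or placebo) in the LR and HR groups will be analyzed using a two-way" repeated-measures ANOVA, with Bonferroni-corrected pairwise comparisons. LR and HR are explicitly compared with each other only on baseline characteristics.
- **Design and aims.** Study overview and design makes NAC against placebo a crossover comparison, so treatment varies within participant. The end of the Background gives the effect of NAC as the objective. The Discussion paragraph of the Abstract adds the question whether regeneration depends on basal satellite-cell content.

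**The concern.** A sample-size statement should let the reader repeat the calculation and see which planned test it supports. This one appears to do neither. The between factor that was sized (LR/HR) is absent from the planned ANOVA, and the treatment factor is absent from the power calculation. The listed inputs also do not seem to lead to the stated number.

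What is at stake is how the results are read. Someone who takes 0.95 as the power of the NAC-placebo comparison, or of the comparison of NAC effects between LR and HR, could treat a null result as evidence of no effect. The document supports neither reading.

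**Working it through.** **1. Does the stated figure follow from the stated inputs?**

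Inputs from the protocol: f = 0.55, α = 0.05, target power 0.95, k = 2 groups, ρ = 0.5, ε = 1. Two assumptions are needed. First, 0.55 is Cohen's f, the metric this test takes. Second, the number of measurements m is one of 2, 3, 4, 6 or 8 (two trials; three or four time points; or all trial-by-time cells).

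For the within-between interaction with total N:

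λ = f²·N·m/(1 − ρ), df1 = (k − 1)(m − 1), df2 = (N − k)(m − 1); power is the upper tail of the non-central F beyond its 5% critical value.

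Example, m = 4, N = 10: λ = 0.3025 × 10 × 4/0.5 = 24.2, df1 = 3, df2 = 24, power 0.978. With N = 8, λ = 19.36 and power is 0.926.

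| m | smallest total N (equal groups) | per group | power at that N | power at N = 20 |
|---|---|---|---|---|
| 2 | 14 | 7 | 0.965 | 0.996 |
| 3 | 12 | 6 | 0.978 | > 0.999 |
| 4 | 10 | 5 | 0.978 | > 0.999 |
| 6 | 8 | 4 | 0.981 | > 0.999 |
| 8 | 6 | 3 | 0.959 | > 0.999 |

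No m gives 20 in total, so the figure is not reproduced. A total of 20 appears only on departing from these inputs: leaving out the listed correlation (λ = f²·N·m, m = 3: N = 20, power 0.964), reading 0.55 as a standardised difference d, so f = 0.275, with m = 8 (N = 20, power 0.960), or using four groups with m = 2 (N = 20, power 0.966). The dropout step is right: 10/0.85 = 11.8, rounded up to 12.

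**2. Is the sized test a planned test?**

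| | power calculation | planned analysis |
|---|---|---|
| between-participant factor | LR/HR | none named; ANOVA in the LR and HR groups |
| within-participant factor(s) | not named | time and trial |
| effect tested | LR/HR × within factor | time and trial effects |

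The two do not match.

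**3. Can the power for NAC against placebo be worked out from the document?**

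Not without knowing what 0.55 measures. For the trial × time interaction in one stratum with n = 10 and b time points, λ = f²·n·2b/(1 − ρ), df1 = b − 1, df2 = (n − 1)(b − 1).

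- 0.55 as f: power above 0.999 for b = 3 or 4.
- 0.55 as d (f = 0.275): power 0.70 for b = 3 and 0.78 for b = 4.
- 0.55 as a paired dz at one time point: power 0.34 with n = 10 and 0.65 with n = 20.

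**4. What can 10 completers per group detect?**

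Two-sided α = 0.05, one time point, no multiplicity adjustment, no period effect, non-central t. The NAC-placebo contrast has non-centrality dz·√n on n − 1 df. The LR-HR difference in that contrast has non-centrality δ·√(n/2) on 2n − 2 df, with δ in SDs of the within-person difference.

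| contrast | 80% power | 95% power |
|---|---|---|
| NAC − placebo, one stratum, n = 10 | dz ≈ 1.00 | dz ≈ 1.29 |
| NAC − placebo, pooled, n = 20 | dz ≈ 0.66 | dz ≈ 0.85 |
| LR − HR difference in NAC effect, 10 per group | δ ≈ 1.33 | δ ≈ 1.71 |

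At δ = 0.8 the non-centrality is 0.8 × √5 = 1.79 on 18 df, and power is about 39%.

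**The case against.** **The arithmetic slip errs on the safe side.** Ten per group is more than the inputs require, and with 20 participants the test computed has power of at least 0.996. This stands. A reader might infer from the failed reproduction that the trial is too small, but the failure does not show that.

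**Sizing on LR/HR is not arbitrary.** The Abstract asks whether regeneration depends on basal satellite-cell content, so an LR/HR comparison answers a stated question, and the fault may lie in an analysis paragraph that omits the factor. This also stands, and the fix allows for it. It does not remove the mismatch: a two-way ANOVA whose factors are time and trial has no third factor, even if the mention of the LR and HR groups is read generously.

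**Three stronger readings are tempting, and the document does not support them.**

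- That only very large effects are detectable. Pooled over 20 completers, dz of about 0.66 is detectable with 80% power. At a correlation of 0.5 the SD of the within-person difference equals the single-occasion SD, so this lies in the protocol's own medium band (0.50–0.79).
- That 0.55 is a NAC-against-placebo effect put into the wrong test. The protocol says the power analysis drew on earlier NAC studies. It does not say which contrast or metric 0.55 represents.
- That a total of 10 was misread as 10 per group. This fits m = 4, but m is not stated, so it is only a possible explanation.

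**Conclusion.** The point holds in two parts. First, the power of 0.95 is attached to an LR/HR interaction that the analysis paragraph does not name, so it belongs to no planned test and none is stated for NAC against placebo. This follows from the text alone and is the more important part. Second, 10 per group does not follow from the listed inputs for any of the numbers of measurements tried. They give 6 to 14 in total, on the assumption that 0.55 is Cohen's f.

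Whether the trial is adequately powered for NAC against placebo cannot be settled from the document, because the metric and contrast behind 0.55 are missing. What can be said is what 10 completers per group detect. The LR-HR comparison of NAC effects is the weakest of these, with about 39% power at 0.8 SD, the value at which the protocol starts to call an effect large (equating the two scales again assumes a correlation of 0.5). The detectable effects are for single-time-point, unadjusted contrasts and are not the power of the omnibus ANOVA.

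**What to change.** Keep at least 12 per group and rewrite the sample-size paragraph.

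1. State the test, its within factor, the number of measurements, the effect-size metric, and whether N is a total or per group, so that the inputs reproduce the number.
2. Replace the power claim with the effects detectable for the within-participant NAC-placebo contrast at 10 completers per group, labelled as a single time point without adjustment: dz about 1.00 (80%) and 1.29 (95%) within a stratum, about 0.66 and 0.85 pooled.
3. Because dependence on basal satellite-cell content is a stated question, add the LR/HR-by-trial (by time) interaction to the planned model. State that an LR-HR difference in the NAC effect must be about 1.33 SD (80%) or 1.71 SD (95%) of the within-person difference, with about 39% power at 0.8 SD.

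The cost is a rewritten paragraph and one added model term, with no extra participants. The stated power becomes less favourable. The Trial status section says that the trial has not commenced, so the change can be made before outcome data exist.

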## Methods/design

### Study overview and design

The methods and ethics of the present study have been approved by the Institutional Review Board of the University of Thessaly (ref. number 1387) and procedures are in accordance with the Declaration of Helsinki, as revised in 2013. The SpEED study incorporates a randomized, two-trial (NAC vs placebo), cross-over, double-blind, repeated-measures design. Participants who will fulfill the inclusion criteria will have their body mass, height, resting metabolic rate (RMR), body composition, muscle strength, soreness and maximal oxygen consumption (VO_2max_) measured. Since protein and antioxidant consumption as well as systematic physical activity (PA) and/or exercise may affect SCs responses and/or redox status, participants’ daily nutrient intake (via a 7-day diet recall with emphasis on protein and antioxidant intake) and PA levels (via accelerometry instrumentation) will be monitored for a week before the inception of the study [24–26]. Then, a 2-week adaptation period (only before the first trial) will be applied to adjust (through a balanced diet, using RMR values and daily energy expenditure measurements) protein and antioxidant intake at the levels required by current Recommended Dietary Allowances (RDAs) (0.8–1 g of protein/kg/day; 900 mg/day of vitamin A; 90 mg/day of vitamin C; 600 IU/day of vitamin D; 15 mg/day of vitamin E; 11 mg/day of zinc; 400 mg/day of magnesium and 55 mg/day of selenium) [27, 28]. This dietary protocol will be designed and implemented by a registered dietician. During the same time-frame, familiarization with experimental procedures will be provided.

Evidence exists that skeletal muscle growth and myogenic potential is directly related to its basal SCs content [24, 29]. As such, volunteers will provide a resting (they will abstain from any exercise or intense PA for at least 5 days prior to sampling) muscle biopsy sample (baseline sampling) from their vastus lateralis muscle (of their dominant limb) and based on its SCs content will be stratified to either high (HR) or low (LR) respondents. Participants will be stratified as HR or LR using a K-means cluster analysis. Blood sampling and performance measurements will also be performed at baseline.

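### Normality tests choose between two analyses that answer different questions, and the rank fallback has no trial-by-time test and ignores the crossover pairing

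*Protocol article*

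**What the plan says.** All of the rules below are in the Protocol article, section *Statistical analyses and Power calculation*.

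- Gate: "Data normality will be examined using the Kolmogorov-Smirnov and the Shapiro-Wilk tests". Then "If our data sets follow normal distribution, parametric tests will be applied", and otherwise "If the data normality is violated, non-parametric tests will be applied".
- Parametric route: time and trial comparisons in the low (LR) and high (HR) respondent groups "will be analyzed using a two-way repeated-measures ANOVA test with a Bonferroni correction for pairwise comparisons".
- Rank route, time: comparisons within each trial "will be analyzed using a Friedman test accompanied by Wilcoxon signed-rank test for pairwise comparisons".
- Rank route, trial: NAC against placebo "will be analyzed using a Kruskal-Wallis test accompanied by a Mann-Whitney" U test for the pairwise comparisons.

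The section *Study overview and design* describes a "randomized, two-trial (NAC vs placebo), cross-over, double-blind, repeated-measures design". Every participant therefore supplies both a NAC value and a placebo value. That section places muscle and blood sampling in each trial before exercise and at 2 and 8 days after it. NAC or placebo starts with a 7-day loading phase, so the pre-exercise sample is already on treatment.

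**The concern.** The two routes are presented as parametric and non-parametric versions of one analysis, but they are not equivalent.

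The stated objective is the effect of NAC on satellite-cell responses after muscle damage. With samples before and after exercise in both trials, a direct expression of that objective is whether the change after exercise differs between NAC and placebo. The two-way ANOVA supplies that contrast. In the rank route, Friedman looks at time inside one trial, and Kruskal-Wallis/Mann-Whitney compares the trials without reference to change from pre-exercise.

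The rank route also drops the pairing. Kruskal-Wallis and Mann-Whitney are independent-samples tests, whereas the crossover exists so that each participant serves as his own control.

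The choice between the routes is made by significance tests on about 10 to 12 people per group. At that size a pass says little about the distribution, and some failures are chance. Two primary markers with similar behaviour could end up with different hypotheses tested and different power.

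**Working it through.** **Inputs from the article.** Two trials by three time points (pre-exercise, 2 days, 8 days) give 6 cells per group. The minimum is 10 per group; with 15% dropout, 10/(1 − 0.15) = 11.76, which the article gives as 11.8 and raises to at least 12. The correlation among repeated measures is 0.5. The primary list comes to 21 markers if Pax7 and MyoD are split by fibre type: 4 satellite-cell, 2 macrophage, 5 mRNA, 6 protein and 4 oxidative-stress.

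**Assumptions, not in the article.** Equal variances and equal correlations across cells, tests at 5%, the size and timing of effects, the degree of skew, and what triggers the switch. The article gives no figure of its own on this point to reproduce.

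**Step 1. What each route tests.**

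| Question | Parametric route | Rank route |
|---|---|---|
| Change over time within a trial | yes | Friedman/Wilcoxon, paired |
| NAC against placebo | yes, within participant | Kruskal-Wallis/Mann-Whitney, unpaired |
| Does the change differ between trials? | yes, by implication of a two-way ANOVA | no test |

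**Step 2. Can the two Friedman results be compared instead?** No NAC effect was simulated, with the same assumed 1 SD time response in both trials. Friedman was significant in exactly one of the two trials in 26% of runs at n = 12 and 42% at n = 10. That pattern invites the conclusion that NAC changed the response when it did not.

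**Step 3. Cost of ignoring the pairing.** For a NAC-placebo difference in means, the true variance is 2σ²(1 − ρ)/n. An unpaired test assumes 2σ²/n. At ρ = 0.5 the true variance is half the assumed one, so the unpaired test is conservative. Simulated at n = 12, with a NAC effect at day 2 only:

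| Effect at day 2 | Mann-Whitney at day 2 | Paired signed-rank at day 2 | Trial-by-time ANOVA test |
|---|---|---|---|
| none (type I error) | 0.011 | 0.035 | 0.050 |
| 0.8 SD | 0.43 | 0.69 | 0.47 |
| 1.0 SD | 0.68 | 0.86 | 0.67 |
| 1.2 SD | 0.83 | 0.96 | 0.82 |

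A repeat simulation gave about 0.65 against 0.85 at 1 SD. At n = 10 and 1 SD the figures are 0.53 and 0.78. The like-for-like comparison is between the second and third columns. The last column tests a different hypothesis; it shows what the parametric route offers and the rank route lacks. A rank version of that contrast is feasible: Friedman on the within-person NAC-minus-placebo differences has power 0.39, 0.57 and 0.71 at the same three effects.

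**Step 4. How often the switch occurs (n = 12, one group).**

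| Trigger rule | Truly normal data | Log-normal, CV 30% |
|---|---|---|
| One Shapiro-Wilk test per marker | about 5% | about 14% |
| Both named tests must reject in the same cell, any of 6 cells | about 13% | about 36% |
| Shapiro-Wilk in any of 6 cells | about 25% | about 57% |

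For six independent cells, 1 − 0.95⁶ = 0.265, so 25% with correlated cells is as expected. At CV 50% the any-cell figure is about 81%. Shapiro-Wilk and Kolmogorov-Smirnov (with the Lilliefors correction) disagreed in 10% to 19% of log-normal samples.

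With one test per marker, the expected number of the 21 markers sent to the rank route is 21 × 0.05 ≈ 1 if all are normal. It is 21 × 0.55 ≈ 12 at log-SD 0.8, and 21 × 0.71 ≈ 15 at log-SD 1.0.

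**The case against.** A reader might infer that markers sent to the rank route are never tested on the trial's own question. The article does not support that. The rank route includes a NAC-against-placebo comparison, and in a randomized crossover such a comparison at days 2 and 8 bears directly on whether NAC alters the response. What is missing is the comparison of change, together with the pairing.

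The article also does not name trial-by-time as its primary contrast. Even the parametric route is worded as time and trial effects, and the interaction is only implied. Because loading begins 7 days before exercise, an effect on muscle glutathione, for example, could be present in the pre-exercise sample. It would then appear in the trial effect and could be missed by the interaction. This stands, and it shapes the fix: both contrasts must be reported.

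A reader might also infer that many primary markers will be switched, one by one. The article speaks of data sets, so marker by marker is a natural reading but not its wording. The number runs from about 1 to about 15 of 21, depending on assumed skew. High switch rates for strongly skewed data are what the gate was built to produce, not a malfunction.

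How disagreement between the two tests is resolved, and whether cells or residuals are tested, are details that an article may leave to a fuller plan; they are not part of this point. The sensitivity analyses that the article promises do not answer it, since nothing says that they would supply the missing contrast or restore the pairing.

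The objection does not reach the named tests. They are fixed in the text, and the fallback built from them is not a counterpart of the ANOVA.

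**Conclusion.** The point holds in this form: normality pre-tests in groups of about 10 to 12 select between two analyses that do not answer the same question, and the rank fallback is the poorer one. It has no test of whether the post-exercise change differs between trials, and it applies independent-samples tests to paired data.

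Under a correlation of 0.5 and n = 12, the unpaired test has a true error rate near 0.01 and loses about 13 to 26 percentage points of power against a paired rank test, for effects of 0.8 to 1.2 SD (0.69 − 0.43 = 0.26; 0.86 − 0.68 = 0.18; 0.96 − 0.83 = 0.13). The risk in that test is missed effects rather than false positives. False claims can arise if the two Friedman results are compared informally (26% discordant at n = 12 with no NAC effect and a 1 SD time response).

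The switch frequency cannot be fixed from the article: about 5% to 25% for normal data, and more with skew. The defect in the fallback does not depend on that frequency. The section should be changed before the analysis.

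**What to change.** In *Statistical analyses and Power calculation*:

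1. Remove the normality gate.
2. Pre-specify one paired within-participant model for every marker, with trial, time and trial-by-time. Report both the trial effect and the trial-by-time contrast, because the pre-exercise sample follows 7 days of loading.
3. Fix the scale in advance: a log scale for skewed positive markers such as mRNA fold changes and densitometry, with a stated rule for zero cell counts.
4. Replace the rank route by a signed-rank or permutation test on two quantities per participant: the NAC-minus-placebo value, and the NAC-minus-placebo difference in change from pre-exercise. Run it for all markers as a pre-specified sensitivity analysis, not as a switch triggered by the data or by residual checks.

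The cost is wording only. No extra samples, visits or participants are needed, and the article states that the trial has not commenced. The downside is that log-scale results are reported as ratios, and that the zero rule has to be chosen and justified beforehand.

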**Discussion:**

This study is designed to investigate the impact of redox status on SCs mobilization and thus skeletal muscle potential for regeneration under conditions of aseptic inflammation induced by exercise. Findings of this trial should provide insight into (1) molecular pathways involved in SCs recruitment and muscle healing under conditions of aseptic skeletal muscle trauma present in numerous catabolic conditions and (2) whether skeletal muscle’s potential for regeneration depends on its basal SCs content.

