Only two studies have examined the effectiveness of antioxidant supplementation on skeletal muscle healing and the inflammatory response in primary cultured cells and rat gastrocnemius muscle demonstrating that polyphenol administration enhances SCs activation and evokes an earlier appearance of M2 macrophages promoting an anti-inflammatory phenotype [19, 20]. However, no studies have investigated, so far, the effect of redox status perturbations on SCs responses and myogenic potential following aseptic trauma in human skeletal muscle. A powerful antioxidant that has been in clinical and sports performance practice for several decades is *N*-acetylcysteine (NAC). NAC is a thiol donor, non-specific antioxidant with a binary antioxidant role: Firstly, NAC directly scavenges a number of reactive oxygen species (ROS) and secondly, it produces reduced cysteine (Cys) by deacetylation, which supports the biosynthesis of endogenous reduced glutathione (GSH) via the activity of γ-glutamylcysteine synthase [21]. GSH plays a pivotal role in cellular metabolism and especially in terms of stem cells’ oxidative defense, activity, survival and self-renewal under conditions of increased OXS and ROS production [22]. Low to moderate ROS levels control physiological cellular signaling pathways and facilitate muscle growth and development while high ROS levels impair myogenesis and cause cell death through apoptotic and/or necrotic mechanisms (e.g., NF-kB signaling) [23]. We hypothesize that NAC administration following aseptic muscle trauma, characterized by severe inflammation and high levels of ROS, will alleviate the increase in oxidative stress by decreasing ROS activity levels, resulting in an optimal intracellular redox environment, favoring the activity (activation, proliferation, differentiation and fusion) of SCs and thus facilitating muscle’s regenerative process and adaptation following muscle injury. Thus, the objectives of this clinical trial are to examine the effects of redox status perturbation (via NAC administration) on the intracellular pathways responsible for SCs responses following aseptic muscle trauma induced by damaging exercise.

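### The trial is sized on an LR/HR interaction, but the planned time-by-trial analysis has no group term, so the sized test is not the planned test

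*Protocol article*

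**What the plan says.** All references are to the protocol article.

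- **Purpose.** The abstract's Discussion paragraph lists, as the second of two expected insights, "whether skeletal muscle’s potential for regeneration depends on its basal SCs content". Study overview and design gives the reason for grouping: "Evidence exists that skeletal muscle growth and myogenic potential is directly related to its basal SCs content". The objectives sentence at the end of Background is narrower. The trial is to "examine the effects of redox status perturbation (via NAC administration) on the intracellular pathways responsible for SCs responses", with no mention of basal SC content.
- **Sizing.** Statistical analyses and Power calculation describes a two-way repeated-measures ANOVA, within-between interaction. The inputs are effect size 0.55, alpha 0.05, power 0.95, two groups (LR and HR), correlation 0.5 and non-sphericity correction 1. The result is 10 per group, raised to 12 for 15% dropout.
- **Outcome analysis.** The same section states: "Time- and trial-effect comparisons within and between trial (NAC or placebo) in the LR and HR groups will be analyzed using a two-way" repeated-measures ANOVA, with Bonferroni-corrected pairwise comparisons.
- **Non-parametric branch.** "Time-effect comparisons within trial (NAC or placebo) in the LR and HR groups will be analyzed using a Friedman test" with Wilcoxon follow-up. NAC is compared with placebo by Kruskal-Wallis and Mann-Whitney tests, again within the two groups.
- **LR versus HR.** The only explicit test between the groups is on baseline characteristics.

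**The concern.** In this crossover every participant receives both NAC and placebo, so time and trial are both within-person factors. Together they use up a two-way model. LR/HR is then a label for the subset analysed and not a term in the model. Neither a group x time nor a group x trial x time interaction is named for any outcome.

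The design pays for that comparison. It takes a muscle biopsy from 40 to 60 men to form the groups and sizes the trial on an interaction with group. If the analysis is followed as written, whether the response depends on basal SC content has no valid test. A reader of the results would be left to compare one group's findings with the other's, which readily suggests a difference where there is none.

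**Working it through.** **1. The two models side by side.**

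| | Between-person factor | Within-person factors | Term of interest |
|---|---|---|---|
| Power calculation | LR/HR | repeated measurements | within-between interaction |
| Outcome ANOVA | none named | time, trial | time and trial comparisons |
| Non-parametric branch | none named | time, or trial | time within trial; NAC versus placebo |

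A two-way group-by-time model leaves out trial, and a two-way time-by-trial model leaves out group. The question needs all three factors, and the article nowhere names them together.

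**2. The plan's own sample size.** The dropout step reproduces: 10/(1 - 0.15) = 11.76, so 12 per group. (The article prints 11.8.)

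The figure of 10 per group can be neither confirmed nor rejected, because the number of repeated measurements m and the effect-size convention are not stated. I used a noncentral F with k = 2 groups, df1 = (k - 1)(m - 1) and df2 = (N - k)(m - 1). I read 0.55 as Cohen's f, which is an assumption.

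- With lambda = f² x N x m/(1 - rho), the total N for 95% power is 14, 12, 10, 8, 8, 8, 6 for m = 2 to 8. For m = 4 and N = 10, lambda = 0.3025 x 10 x 4/0.5 = 24.2. No m gives 10 per group.
- With lambda = f² x df2 (effect size taken from partial eta-squared), the total N is 48, 30, 24, 20, 18, 16, 14. For m = 5 and N = 20, lambda = 0.3025 x 72 = 21.78, which gives exactly 10 per group.

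The mismatch in step 1 does not depend on this figure.

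**3. What comparing within-group results would do.** The protocol gives no dz, so the values here are assumed. The model is a paired t-test on one NAC-minus-placebo contrast, n = 12 per group, two-sided 0.05, noncentrality dz x √12, with the same true effect in both groups. If p is the power in one group, the chance that exactly one group is significant is 2p(1 - p).

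| dz | p | 2p(1 - p) |
|---|---|---|
| 0.3 | 0.158 | 27% |
| 0.5 | 0.353 | 46% |
| 0.6 | 0.475 | 50% |
| 0.8 | 0.714 | 41% |
| 1.0 | 0.883 | 21% |
| 1.2 | 0.965 | 7% |

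**4. What a direct test can detect.** Comparing LR with HR on each person's NAC-minus-placebo contrast is a two-sample t-test with 2n - 2 degrees of freedom and noncentrality d x √(n/2), where d is in SD units of that contrast.

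- 12 per group: d = 1.20 for 80% power, 1.55 for 95%.
- 10 per group: d = 1.33 for 80% power, 1.71 for 95%.

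**5. The NAC effect itself.** If the groups are analysed separately, the NAC effect detectable with 80% power is dz = 0.89 (n = 12). In one analysis of all 24 participants it is dz = 0.60.

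**The case against.** The strongest reply is that group is implied. The power paragraph and the analysis paragraph both use the name two-way repeated-measures ANOVA, and the first gives LR and HR as its groups. The article also never says in so many words that the groups will be analysed separately. That much stands: separate analysis is the more natural reading but not an explicit statement. It does not remove the mismatch, because a two-way model cannot hold group, trial and time, and the two factors tied to the outcome analysis are time and trial. The non-parametric branch points the same way.

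Several stronger readings are tempting, and the article does not support them:

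- *A formal objective goes untested.* The abstract's aim, the objectives sentence and the research hypothesis in the Discussion concern only redox status and NAC. Basal SC content is an expected insight and the reason for grouping.
- *Contrasting p-values is all the plan leaves.* Hedges' g with 95% confidence intervals is planned for all dependent variables, so magnitudes can be set side by side. That is still not a test of difference. Nor does the article say that a difference will be inferred from significance in one group only.
- *The 21% to 50% is this trial's error rate.* It comes from an assumed dz and a single paired test, not the planned ANOVA. 50% is the maximum of 2p(1 - p), and the figure is 7% at dz = 1.2.
- *The grouping method will fail.* The article says at least 12 "participants per group (LR vs HR) will be selected from the initial sample" by k-means. K-means partitions a sample and guarantees no cluster size, so that sentence deserves tidying. How often a cluster would fall short of 12 depends on an SC distribution the article does not give. Selecting the 12 lowest and 12 highest men instead is not a needed remedy. It changes who enters the trial and increases regression to the mean on Pax7+ content, which is also a primary outcome.

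Pearson correlations among variables are planned as well, but without naming the variables. They do not test whether the NAC effect differs by group.

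**Conclusion.** The point holds. The interaction used to size the trial is not carried into the outcome analysis, and no LR-versus-HR contrast on any outcome is specified in either branch. This is not detail left to a statistical analysis plan, because the article itself fixes a two-way time-and-trial model.

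The conclusion rests on the wording alone and needs no assumed effect size. The consequence is confined to the basal-SC question: the NAC comparison remains analysable, though less precisely if the groups are analysed separately. Under the stated assumptions, a spurious one-group-only pattern occurs in 21% to 50% of trials for dz of 0.5 to 1.0. A direct group comparison at 12 per group reliably finds only large differences, about d = 1.2 at 80% power.

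**What to change.** Replace the outcome analysis with one mixed model, or a three-factor mixed ANOVA, over all participants. LR/HR is the between-person factor, trial and time are the within-person factors, and the interactions are included. Then:

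1. Name group x time and group x trial x time as the tests of the basal-SC question.
2. Report the NAC effect (trial x time) from this all-participant model, with within-group results as descriptive.
3. Rewrite the power paragraph for the named interaction, stating the number of repeated measurements and the effect-size convention.
4. As a minor wording point, say how at least 12 per group will be obtained, since k-means alone does not ensure it.

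The cost is a few sentences. Trial status says that the trial has not commenced, so the change can precede any outcome data. The downside is limited power for the group interaction at 12 per group (about d = 1.2 on the NAC-minus-placebo contrast for 80%). The protocol should state this, so that a non-significant interaction is not read as evidence of equal response.
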